# A double-blind randomised controlled investigation into the efficacy of Mirococept (APT070) for preventing ischaemia reperfusion injury in the kidney allograft (EMPIRIKAL): study protocol for a randomised controlled trial

**DOI:** 10.1186/s13063-017-1972-x

**Published:** 2017-06-06

**Keywords:** Delayed graft function, Mirococept, Complement inhibitor, Ischaemia reperfusion injury, Kidney transplantation

## Abstract

**Background:**

Delayed graft function (DGF) is traditionally defined as the requirement for dialysis during the first week after transplantation. DGF is a common complication of renal transplantation, and it negatively affects short- and long-term graft outcomes. Ischaemia reperfusion injury (IRI) is a prime contributor to the development of DGF. It is well established that complement system activation plays a pivotal role in the pathogenesis of IRI. Mirococept is a highly effective complement inhibitor that can be administered ex vivo to the donor kidney just before transplantation. Preclinical and clinical evidence suggests that Mirococept inhibits inflammatory responses that follow IRI. The EMPIRIKAL trial (REC 12/LO/1334) aims to evaluate the efficacy of Mirococept in reducing the incidence of DGF in cadaveric renal transplantation.

**Methods/design:**

EMPIRIKAL is a multicentre double-blind randomised case-control trial designed to test the superiority of Mirococept in the prevention of DGF in cadaveric renal allografts, as compared to standard cold perfusion fluid (Soltran®). Patients will be randomised to Mirococept or placebo (Pbo) and will be enrolled in cohorts of *N* = 80 with a maximum number of 7 cohorts. The first cohort will be randomised to 10 mg of Mirococept or Pbo. After the completion of each cohort, an interim analysis will be carried out in order to evaluate the dose allocation for the next cohort (possible doses: 5–25 mg). Immunosuppression therapy, antibiotic and antiviral prophylaxis will be administered as per local centre protocols. The enrolment will take approximately 24 months, and patients will be followed for 12 months. The primary endpoint is DGF, defined as the requirement for dialysis during the first week after transplantation. Secondary endpoints include duration of DGF, functional DGF, renal function at 12 months, acute rejection episodes at 6 and 12 months, primary non-function and time of hospital stay on first admission and in the first year following transplant. Safety evaluation will include the monitoring of laboratory data and the recording of all adverse events.

**Discussion:**

The EMPIRIKAL trial is the first study to evaluate the efficacy of an ex vivo administered complement inhibitor (Mirococept) in preventing DGF in cadaveric human renal transplantation. Mirococept has a unique ‘cytotopic’ property that permits its retention in the organ microvasculature.

**Trial registration:**

ISRCTN registry, ISRCTN49958194. Registered on 3 August 2012.

**Electronic supplementary material:**

The online version of this article (doi:10.1186/s13063-017-1972-x) contains supplementary material, which is available to authorized users.

## Background

Ischaemia reperfusion injury (IRI) is a consequence of kidney transplantation that often progresses to the clinical diagnosis of delayed graft function (DGF). DGF has traditionally been defined as the requirement for dialysis within the first week after transplantation, although more than 10 definitions have been recorded in the literature [1]. Approximately one third of all kidney transplants will develop DGF with this proportion rising to 50% when the organ is retrieved by donation after circulatory death (DCD) [2]. DGF is associated with higher rates of acute rejection and with reduced long-term kidney survival even in patients who did not undergo rejection [3]. In this regard, strategies to prevent IRI and the subsequent development of DGF are of paramount importance for improving renal graft outcomes.

The reperfusion of the ischaemic kidney induces a proinflammatory reaction in which activation of the complement system plays a central role [4]. Complement-depleted or deficient animals exhibit reduced post ischaemic acute renal failure and chronic nephropathy [4–6]. Recent studies have indicated that locally synthesised complement components play a more important role in activating local inflammatory processes and mediating graft immunogenicity than complement components from the systemic circulation [7]. The central step in complement activation is the cleavage of C3 to C3b by C3 convertase. Membrane-bound C3b binds to activated factor B and forms the C3 alternative pathway convertase enzyme, resulting in further C3 cleavage to C3b. The primary trigger is now believed to be the lectin pathway, followed by amplification through the alternative pathway, both pathways converging on the central component C3 [8]. This ultimately leads to C5a- and C5b-9-mediated injury of the renal tubule, and C3a- and C5a-mediated enhancement of the recipient immune response [9, 10]. In vivo protection against aberrant complement activation is prevented by the natural regulators of complement activation (RCAs), which can be membrane bound (e.g. CD35 — also known as CR1 — CD46 and CD55) or soluble (e.g. factor H). RCAs act via two mechanisms: one by inhibiting C3 and C5 convertases by accelerating their decay and the other by acting as cofactors for factor I-mediated proteolysis of C3b/C4b to the inactive iC3b and C3d and C4d respectively [11]. Microarray analyses of human renal graft biopsies before transplantation have shown a negative correlation between complement gene expression and graft function in the early (2–3 days) and late (2–3 years) post-transplant period [12]. Of note, the duration of cold ischaemia was positively associated with the level of complement gene expression. This relationship was previously demonstrated in a mouse renal isograft model where intrarenal C3 mRNA level increased in relation to the duration of cold ischaemia time (CIT) [13]. Intriguingly, in this model, local C3 — mostly produced by the tubular epithelium — was essential for complement-mediated reperfusion damage [13].

Together, these mechanisms provide a rationale for local therapeutic manipulation of C3 function during early transplantation in order to improve the short- and possibly longer-term outcomes of renal grafts. The local control of complement activation would have the advantage of providing graft protection whilst avoiding the systemic abrogation of the complement system and the consequent impairment of recipient immune defences.

Mirococept (APT070) is a highly effective complement inhibitor which is derived from human CR1 (CD35). It consists of three functional units: the terminal three domains of CR1 which contain its biological activities, a membrane-associating peptide and a membrane-inserting myristoyl group [14]. The last two units permit the binding to and insertion into the cell membrane. Mirococept is unique in that it is engineered to bind to cell surfaces in bulk [15] and can block the complement system at the C3 level. It does not inhibit proteases generally, and its action is restricted to the complement system.

Mirococept has been shown to inhibit complement activation and the subsequent inflammatory reaction in a variety of experimental diseases that are associated with complement activation such as rheumatoid arthritis [16], Guillain-Barre syndrome [17], intestinal ischaemia [18], myocardial ischaemia [19] and kidney transplantation [6, 20]. We previously developed a strategy to administer Mirococept in the donor kidney, thereby avoiding any undesirable consequences from systemic complement inhibition [6]. After being administered to the kidney ex vivo, via the renal artery, Mirococept localises to the graft endothelial and epithelial cells. In a rat transplant IRI model we showed that local inhibition of complement activation within the graft by Mirococept reduced complement-mediated injury [6]. Specifically, Mirococept reduced inflammatory injury and allograft rejection, thus improving graft function in the short (throughout the first week) and long term (20 weeks). As these results were obtained after the relatively short ischaemia time of 30 min, we further evaluated Mirococept efficacy in a rat renal transplantation model of prolonged cold ischaemia (16 h). Similarly to our previous findings, Mirococept reduced ischaemia reperfusion damage and inflammation by inhibiting complement activation at the C3 level [20]. It also increased the number of donor organs that survived after transplantation by at least twofold.

The safety of Mirococept has been documented by preclinical, phase I and phase IIa clinical studies (see section on Safety evaluation and recording of adverse events). Moreover, in the phase IIa clinical trial where Mirococept or placebo (Pbo) was administered to the kidney ex vivo before transplantation, a trend was observed toward lower creatinine in the Mirococept group [21]. The aim of the current trial is to provide further evidence supporting the efficacy of Mirococept in preventing DGF in cadaveric human renal transplantation.

## Methods/design

### Trial design

This is a multicentre, double-blind, randomised case-control trial, designed to test the superiority of Mirococept in the prevention of DGF in cadaveric renal allografts, as compared to standard cold perfusion fluid (Soltran®). Patients will be randomised to treatment or Pbo, and randomisation will be carried out in blocks and stratified by centre, type of donor, i.e. Donation after Circulatory Death (DCD)/Donation after Brain Death (DBD), and whether the organ has been machine pumped. Immunosuppression therapy, antibiotic and antiviral prophylaxis will be administered as per local centre protocols. In order to estimate the dose-response curve and obtain the minimum effective dose (MED), we will use an adaptive design known as the cumulative cohort design (CCD) for dose finding, first described by Ivanova et al. [22, 23]. In most cases this adaptive design is more powerful and effective in finding differences against Pbo and in estimating the dose-response curve, compared to an equal allocation design. This is because the adaptive procedure successfully assigns more patients to Pbo and the target dose, i.e. the MED. Reporting conforms to the Standard Protocol Items: Recommendations for Interventional Trials (SPIRIT) checklist (see Additional file 1).

### Selection of participants, recruiting and consent

The inclusion and exclusion criteria are shown in Table 1. Potential participants will be identified from the active kidney transplant waiting list. After initial screening, eligible participants will be contacted and Patient Information Sheet part A (see Additional file 2 for template copies of the Patient Information Sheet) mailed to the patient’s home address. Participants will be able to discuss the trial with their recruiting site physician and decide whether they want to participate when a donor kidney becomes available. At the time of transplant, all patients will be screened for eligibility on arrival as part of their routine assessment for transplantation. Eligible participants will be given Patient Information Sheet part B and consented on admission (see Additional file 3 for a template copy of the Informed Consent Form) (see Fig. 1: study flowchart).

**Table 1 Tab1:** Inclusion and exclusion criteria

Inclusion criteria	1. Patient must be 16 years of age or older and registered on the kidney transplant list. 2. Patient must be willing to participate in the study and provide written informed consent. 3. Patient must have the ability to comply with the study requirements. 4. Donor must be older than 10 years of age. 5. Patient is on dialysis.
Exclusion criteria	1. Patient is recipient of a living-donor kidney. 2. Patient is a recipient of a DCD kidney Maastricht category 1 or 2. 3. Patient has evidence of current infection with HIV, HBV or HCV. 4. Patient is recipient of a paediatric en bloc or a adult double renal transplant. 5. Any recipient of a multi-organ transplant or a previous recipient of a non-renal solid organ transplant. 6. Females who are pregnant or lactating. 7. Male and female patients not willing to use contraception for at least one month post-transplant. 8. Any planned ABO blood group or HLA antibody-incompatible transplant. 9. Patient is involved in other experimental drug trials.

**Fig. 1 Fig1:**
[figure not shown]
Study flowchart

### Recruitment in cohorts

Patients will be enrolled in cohorts of *N* = 80 with a maximum number of 7 cohorts (maximum number of transplants = 560). Each cohort will be randomised to one of two groups, Pbo or one dose of Mirococept. As originally planned, the first cohort will be randomised to Pbo or 10 mg of Mirococept. After the completion of each cohort, an interim analysis will be carried out in order to evaluate the dose allocation for the next cohort (Fig. 2: recruitment cohorts). Based on the data from previous studies, we will work with five possible doses: 5 mg, 10 mg, 15 mg, 20 mg and 25 mg.

**Fig. 2 Fig2:**
[figure not shown]
Recruitment cohorts

### Randomisation

Recruiting site personnel will be responsible for randomisation of individual patients through the described process. Patients will be randomised to treatment or Pbo with an allocation ratio of (Pbo:drug) 1:2 (i.e. 27 Pbo/53 drug per cohort). Randomisation uses minimisation for the following factors:□ Centre□ Donation after Circulatory Death (DCD) or Donation after Brain Death (DBD)□ Machine pump use

Once ensuring all inclusion and none of the exclusion criteria are met and written informed consent is obtained, the patient must be registered on the MACRO trial database and is assigned a unique patient identifier. The patient can then be randomised, with this patient ID, via SealedEnvelope, an independent web-based company that will be accessible to all the centres via the Internet (https://www.sealedenvelope.com/empirikal/). In the event that a pack number is assigned, but the transplant does not go ahead, the pack is quarantined, in the area predesignated for quarantined kits, until it can be reassigned for use.

### Preparation of the kidney and administration of Mirococept

The following steps are used to prepare the kidney and administer Mirococept:Using a 1000-ml Soltran bag, the first 500 ml will be used to flush the organ prior to administration of the investigational medicinal product (IMP). (N.B University of Wisconsin (UW) solution will affect the bioavailability of Mirococept and is therefore not used.)Machine-pumped organs must not to be placed back on the pump after initial flush with Soltran has been completed.The kidney will be placed in a container of ice slush for bench work.The vials of IMP take approximately 15 min to thaw, and so should be removed from the freezer with sufficient time to allow for this.Whilst the kidney is in ice slush, all five vials of the IMP are drawn up from the patient’s allocated drug kit and added to the remaining 500 ml Soltran (500 ml should be left in the 1000-ml bag following the initial use of 500 ml for the flush). Once the IMP is mixed with the remaining 500 ml of Soltran in the bag, the fluid is then perfused through the kidney via the renal artery (arteries), under 1 m hydrostatic pressure.The perfusion will be conducted via a cannula held in place manually such that as much perfusion solution as possible drains through the kidney.If there is more than one renal artery, and they are of sufficient size, the IMP should be distributed through each of the arteries according to their estimated proportion of the kidney that they vascularise.The administration of IMP should take approximately 15 min.Following perfusion the cannula can be removed and the kidney repacked for cold storage.No post-perfusion flush or arterial or renal vein clamping will be required.

The transplantation procedure will continue in the standard manner, and the patient will be monitored according to standard procedures.

At the Guy’s site only, two biopsy samples will be taken (one half of each core that is taken routinely as part of clinical practice will be used in research): before perfusion with IMP and blood and after perfusion with IMP and blood. The research biopsies will be used to determine the presence of CR1, C3d and membrane attack complex (MAC) deposition. This information will not be available to the clinician, so as to maintain blinding.

### Concomitant medication

Patients in this trial will receive the local standard treatment for those undergoing a renal transplant. This encompasses presurgery medication, general anaesthesia, recovery from anaesthesia, pain control medication and anti-infective therapy (viral, fungal and bacterial). Immunosuppression therapy should be given as per local standard protocol.

Anaesthesia-related medication will not be regarded as concomitant medication.

Other treatments which will not be considered as concomitant medication are:□ Pneumocystis jiroveci pneumonia (PJP, PCP) prophylaxis□ Cytomegalovirus (CMV) prophylaxis□ Tuberculosis (TB) prophylaxis

The use of other medications will be recorded in detail in the patient study MACRO database. Experimental drug therapies will not be allowed for the duration of the trial.

### Research samples

All laboratory investigations that are required are part of the routine management of renal transplant patients, except the following which are additional:□ Serum samples for antibodies to Mirococept□ Serum samples for Mirococept (*at the Guy’s site only*)□ Serum samples for complement activity□ Whole blood samples for RNA bio-markers (*cohort 1 patients only*)□ Plasma samples for symmetric dimethylarginine (SDMA) levels□ Urine samples for markers of tubular damage□ Urine samples for C3a□ Urine samples for RNA bio-markers (*at the Guy’s site cohort 1 patients only*)□ Renal biopsy tissue for research (*at the Guy’s site only*)

Although serum, plasma and RNA do not fall under the Human Tissue Act (HTAct) relevant material, all samples will be processed, tracked and stored according to HTAct 2004 and the European Union Directive Guidelines. The EMPIRIKAL Laboratory Manual gives full details on collection, processing, storage and shipment of research samples (see Additional file 4).

The trial’s assessment schedule is shown in Table 2.

**Table 2 Tab2:**
[figure not shown]
Assessment schedule

Key

Where an ’x’ is contained within a field, this denotes that the associated data is essential and if missed will be classified as a protocol deviation

Where a ’Δ’ is contained within a field, this denotes that the associated data is desirable, and whilst every effort should be made to record these data, missing data will *not* constitute a protocol deviation

*eGFR* estimated glomerular filtration rate, *Hb* haemoglobin, *WBC* white blood cells, *RBP* retinol binding protein, *NAG N*-acetyl-β-d-glucosaminidase, *NGAL* neutrophil gelatinase-associated lipocalin, *CNI* calcineurin inhibitor, *PTLD*, post-transplant lymphoproliferative disorder

### Outcome measurements

#### Primary outcome

The primary outcome is DGF, defined as the requirement for dialysis during the first week after transplantation.

#### Secondary outcomes

The secondary outcomes are as follows:Duration of DGFMean calculated glomerular filtration rate (GFR) (MDRD) at 12 monthsMean calculated GFR (Cockcroft-Gault) at 12 monthsFunctional DGF, i.e. the absence of a decrease in serum creatinine of at least 10% per day for at least 3 consecutive days in the first week post-transplant (not including patients with biopsy-proven acute rejection (BPAR) or calcineurin inhibitor (CNI) toxicity within first week)Primary non-function, defined as a permanent lack of function of the allograft from the time of transplantationArea under the curve (AUC) of the daily serum creatinine days 1–14Biopsy-proven acute rejection at 6 months and 12 months including borderline changesCNI toxicityTime of recipient hospital stay on first admissionTime of recipient hospital stay in first yearGraft 1-year survival (censored and uncensored for death of patient with functioning allograft)Recipient 1-year survival

### Code break

Randomisation data are kept strictly confidential, accessible only to authorised persons not involved in any aspect of the conduct of the trial, until the time of unblinding. At every interim review and at the conclusion of the trial, the occurrence of any emergency code breaks will be determined after return of all code break reports to King’s Health Partners Clinical Trials Office (KHP-CTO). When each cohort has been completed, the data file verified and protocol violations determined, the medication randomisation codes will be broken and made available for interim data analysis.

A 24-h medical information and emergency unblinding service will be provided by the Emergency Scientific Medical Service (ESMS). Code break envelopes will be provided to ESMS. If a request for unblinding is received by ESMS, they will notify the KHP-CTO by fax on the next working day, including information on whether the subject was unblinded or not. Only requests to unblind from a medical doctor will be accepted (e.g. accident and emergency doctor, general practitioner). The KHP-CTO will inform the Chief Investigator (CI) Team and recruiting Principal Investigator (PI) of an unblinding request where appropriate. If the participant has been unblinded, the recruiting PI and CI may not be informed of the treatment allocation unless that information is needed for the participant’s medical care. The decision on whether to inform the recruiting PI will be made by the CI in conjunction with the Trial Statistician. All trial subjects will be issued with a card containing trial identification information and emergency unblinding/medical information contact details.

### Withdrawal of subjects

The subjects will be advised in the Patient Information Sheets and during the consent process that they have the right to withdraw from the study at any time without prejudice, and may be withdrawn at the discretion of the Investigator at any time. In the event that a subject drops out of the trial or is withdrawn from the trial, the appropriate withdrawal electronic Case Report Form (eCRF) will be completed on the MACRO database (if applicable, blood samples should be taken for analysis). Reasonable effort will be made to contact any subject lost to follow up during the course of the trial in order to complete assessments and retrieve any outstanding data. The cases of patients who die during the trial will be assessed by the external data monitoring committee as soon as possible to determine whether the trial should be halted. If the cause of death of a patient is deemed unrelated to the trial, that patient may be replaced in the analysis by another eligible patient.

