### Expected duration of trial: end of study definition

Patient recruitment is expected to take approximately 24 months (including interim reviews), and follow-up will continue until the last recruited patient completes their 12 months follow-up unless the trial is terminated earlier for futility. The trial will be closed when all participants have made their final follow-up visit, the data are entered into the database and all queries resolved and the database locked. All serious adverse events (SAEs) will be followed up for a further 30 days after the stopping of the trial (last patient’s final 1 year follow-up visit date) or until resolution.

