In the present protocol, we do not expect more than approximately 20% of the maximum dose administered to the graft to reach the systemic circulation. At the doses proposed (5–25 mg), this exposure lies in the range of 1–5 mg of drug. Therefore, we do not consider drug-related AEs to be likely.

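### Replacing in the analysis patients whose deaths are judged unrelated conflicts with two survival outcomes and, so far as it is used, biases both towards better survival

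*Protocol article*

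**What the plan says.** In the protocol article, the section Withdrawal of subjects deals with deaths in two steps. Cases of patients who die "will be assessed by the external data monitoring committee as soon as possible to determine whether the trial should be halted". Then, where a death is judged unrelated to the trial, "that patient may be replaced in the analysis by another eligible patient". The section does not say who makes the judgement of relatedness, by what criterion, whether that person is blind to allocation, or when the discretion is to be used.

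The section Secondary outcomes lists "Recipient 1-year survival" and one-year graft survival in two versions, "censored and uncensored for death of patient with functioning allograft". The primary outcome is DGF, the "requirement for dialysis during the first week after transplantation". On duration, "follow-up will continue until the last recruited patient completes their 12 months follow-up".

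The section Safety evaluation and reporting of adverse events expects little systemic exposure and concludes that "we do not consider drug-related AEs to be likely". The section on missing data handles loss to follow-up by censoring or imputation. Replacement is stated only for deaths.

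**The concern.** The rule acts on the analysis and not merely on recruitment. A patient who was randomised and transplanted can be taken out because of something that happened afterwards, and a later recruit put in the vacated place. Three features make this a problem.

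- The event that triggers removal is itself an endpoint. Death is the event for recipient survival and is one of the events for graft survival uncensored for death. Removing patients because they had the event pushes both estimates upwards.
- Removal depends on a judgement of relatedness and on a discretionary choice. Since the authors think drug-related adverse events unlikely, most deaths could be expected to qualify. Under the section Code break, allocation codes are released for interim analysis as each cohort completes, while 12-month follow-up is still running. A late death could therefore be judged after its cohort has been unblinded.
- A patient who dies after the first week already has an observed DGF status. Replacement discards it, together with any graft loss that preceded the death.

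At stake is mainly the between-arm comparison of patient survival and of graft survival with death counted.

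**Working it through.** The plan states no figure that depends on this rule, so there is nothing to reproduce. The size has to be illustrated on assumed rates.

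**Inputs from the protocol article.** Maximum 560 transplants in seven cohorts; 27 placebo and 53 drug per cohort, so 7 × 27 = 189 and 7 × 53 = 371; DGF risk 35% on control and 25% on treatment.

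**Assumptions, not in the document.** One-year mortality m between 2% and 8%; share u of deaths judged unrelated and replaced between 50% and 100%; replacements survive like the other patients.

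**Deaths exposed to the rule.** 560 × 0.02 = 11; 560 × 0.05 = 28; 560 × 0.08 = 45. These are upper limits, since not every death need be replaced.

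**Recipient survival.** Analysed mortality = m(1 − u)/(1 − mu).

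- Overall, with u = 0.9: m = 2% gives 0.002/0.982 = 0.2%; m = 5% gives 0.005/0.955 = 0.5%; m = 8% gives 0.008/0.928 = 0.9%.
- By arm, with true mortality of 3% on placebo and 6% on drug (difference 3.0 points):

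| u | Placebo | Drug | Difference |
|---|---|---|---|
| 0.8 | 0.006/0.976 = 0.61% | 0.012/0.952 = 1.26% | 0.65 points |
| 0.9 | 0.003/0.973 = 0.31% | 0.006/0.946 = 0.63% | 0.33 points |
| 1.0 | 0 | 0 | 0 |

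The shrinkage is on the absolute scale. With the same u in both arms the ratio stays close to 2 (1.26/0.61 is about 2.1), but it rests on far fewer events. At u = 0.9 the expected deaths in the analysis are 189 × 0.00308 + 371 × 0.00634 = 0.58 + 2.35, about 3, against 189 × 0.03 + 371 × 0.06 = 5.7 + 22.3, about 28, if nobody is replaced. If u differs between arms, the ratio is biased as well.

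**Graft survival.** In the uncensored version the deaths component is reduced in the same way. Graft losses in surviving patients remain as events in both versions.

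**DGF.** With true risk p, mortality d1 after DGF and d0 without it, the analysed risk is p(1 − d1·u)/[p(1 − d1·u) + (1 − p)(1 − d0·u)].

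- Assume d1 = 6%, d0 = 2%, u = 1. Control: 0.329/(0.329 + 0.637) = 34.1%. Treatment: 0.235/(0.235 + 0.735) = 24.2%. The 10.0-point difference becomes 9.8.
- No true effect (35% in both arms), u = 0.5 in one arm and 1 in the other, same mortality: 34.5% against 34.1%, a spurious difference of about 0.5 points.
- The same with d1 = 10% and d0 = 3%: 34.2% against 33.3%, about 0.9 points.

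**The case against.** The strongest reply is that the sentence does much less harm than it appears to, on four grounds.

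- **Safety oversight is separate.** Each death goes to the external data monitoring committee, adverse events are recorded from consent, and serious events are followed beyond the end of the trial. This stands. A reader might infer that the rule can hide a safety signal, but the documents do not support that: replacement in an analysis takes no death out of these channels.
- **The endpoints are not emptied.** A reader might infer that the survival outcomes lose all content, or that an excess such as 19 deaths on drug against 4 on placebo would vanish. That example takes 5% of 371 and 2% of 189, opposite ends of an assumed mortality range, and needs every death to be judged unrelated and every option to replace to be taken. Deaths judged related or not replaced stay in, and graft losses in survivors still count. This stands too.
- **DGF is barely touched.** It would go too far to say that the randomised comparison is materially broken for every endpoint. On the assumed rates the DGF difference moves by about 0.2 points, so the primary analysis and the dose decisions based on DGF would change little.
- **The scope is unclear.** Fixed cohorts of 80 suit replacing an early death while a cohort is filling better than replacing one months later. That is fair, and it is why the death counts above are upper limits. But the sentence sets no time limit.

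One defence fails. It may be said that the full protocol or the analysis plan defines the analysis sets. This is not an omission left to another document: the article states a rule about the analysis, and a plan that kept all randomised patients would contradict it.

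**Conclusion.** The rule is wrong as written. It permits a discretionary, judgement-based exclusion of randomised patients on a post-randomisation event, and that event counts in two of the trial's own secondary outcomes. Nothing else in the article puts the removed patients back.

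So far as the rule is used, recipient survival and death-uncensored graft survival are biased upwards, and the absolute between-arm difference in deaths shrinks roughly in proportion to the share replaced. The size rests on mortality and replacement shares that the document does not give, so the figures are illustrations and not predictions. Complete loss of the difference is only the limiting case. The consequence for DGF is minor, though discarding an outcome already observed has no justification.

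**What to change.** Delete the sentence, or at the least strike the words that make the replacement apply in the analysis. In its place state that:

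- every randomised and transplanted patient stays in the analysis in the assigned group;
- deaths are events in recipient survival and in graft survival uncensored for death, and are censored only in death-censored graft survival;
- DGF status observed before death is used;
- any extra recruits are added to the analysed patients and never substituted for them.

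The change is a short amendment. It costs no patients and no data, and it retains outcomes that the present wording would allow to be discarded.
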